### Secondary outcomes

#### Patient satisfaction

To test for non-inferiority in satisfaction with the provided service measured when comparing those patients treated under the old model care compared to those treated under the new model of care, a feedback informed treatment tool will be utilised.

##### Session Rating Scale (SRS)

The Session Rating Scale (SRS) is four-item visual analogue scale with each scale measured between 0 and 10 designed to assess key dimensions of effective therapeutic relationships and global satisfaction with treatment. The SRS is scored by summing score on each of the four scales with a total possible score of 40 [39].

#### Patient, staff and referrer satisfaction

We are particularly interested in incorporating digital intervention into our model of care. Therefore, for those patients assigned to digital intervention in the new model of care, acceptability and relatability of the online program will be measured via post-intervention questionnaires delivered to patients and staff via a RedCap survey. All multidisciplinary staff of the Sleep Disorders Centre employed during the new model of care implementation phase will be send a questionnaire via Microsoft Forms. Note that these questionnaires are modelled on the service evaluation questionnaires from the “Reboot” online pain management program implemented at Queensland Health’s Sunshine Coast Persistent Pain Management Service [31].

### Implementation and evaluation – RE-AIM

To measure the impact of our service change on both patient and service/organisational level outcomes, the evaluation is outlined below with according to the RE-AIM framework (see Table 1).

**Table 1 Tab1:** RE-AIM evaluation framework

Evaluation Question	RE-AIM Domain	Indicator/Measure	Standard/Target	Data Source
*Did patients access care as expected under the new model of care?*	**Reach – The absolute number**,** proportion**,** and representativeness of individuals who are willing** **to participate**	• Percentage of patients agreeing to digital compared to those offered • Patient-reported reasons for declining digital intervention • Percentage of patients referred Direct to Psychology who remain on this pathway • Differences in patient characteristics (age, sex, geographical location, presenting issue) between those agreeing to digital compared to those declining • Number of patients and patient characteristics (age, sex, geographical location, presenting issue) of those assigned to each treatment level • Differences in patient characteristics (age, sex, geographical location, presenting issue) between those referred Direct to Psychology compared to those referred via the standard pathway • Time to start the online program from date of prescription for those assigned to digital intervention • % digital intervention sessions completed for those assigned to digital intervention	> 80% patients offered digital intervention accept digital < 20% patients are referred back to standard care > 80% patients commence within 4 weeks > 80% patients complete digital intervention	Patient qualitative and quantitative surveys Medical Record Patient registration system
*How effective was the model of care in achieving its intended outcomes?*	**Effectiveness** – impact on outcomes and quality of life/economic outcomes	**Primary outcomes** *Service Access Measures* • Average number of occasions of Service within Sleep Psychology service under ‘old’ model compared to ‘new’ model of care • Percentage of new patient activity under ‘old’ model compared to ‘new’ model of care • Average wait-time to access a first appointment with Sleep Psychology from date of referral under ‘old’ model compared to ‘new’ model of care • Average time to discharge from first appointment to final appointment with Sleep Psychology under ‘old’ model compared to ‘new’ model of care • Percentage of patients discharged from psychology *Patient-related Outcomes* • Change scores on clinical outcome measures pre- to post- treatment on clinical outcome measures (ISI, DASS-21, K10 and EQ-5D-5 L) comparing patients treated under ‘old’ model versus ‘new’ model of care • % patients treated adequately at each level of Stepped Care • Differences in patient characteristics (age, sex, geographical location, presenting issue) between those who are adequately treated at each level of the new model of care (moderation analysis) *Economic Outcomes* • Quality-adjusted life year calculations as a measure of cost-effectiveness of the ‘new’ model of care compared to the ‘old’ model of standard care **Secondary outcomes** *Patient satisfaction* • Patient satisfaction measure (SRS) post- treatment comparing patients treated under ‘old’ model versus ‘new’ model of care *Patient satisfaction with digital intervention* • Patient reported ease of access to digital intervention • Acceptability and relatability of the online program/service provided (rated by patients), including: i. motivation to access online treatment (diversion from public hospital services for insomnia treatment) ii. understanding of intervention materials iv. perceived change in sleep problem • Differences in patient characteristics (age, sex, geographical location, presenting issue) between those who complete the digital intervention compared to those who do not complete	Significantly fewer occasions of service under new model of care Significantly greater % new patient appointments under new model Significantly shorter wait-time to first appointment under new model Significantly shorter time to discharge under new model Outcomes are non-inferior under new model of care; upper bound 95%CI on outcome measures is less than MCID MCID is achieved on outcome measures by > 80% patients at each level The ‘new’ model is more cost effective Patient reported satisfaction is non-inferior under new model of care; upper bound 95%CI is less than MCID > 90% patients report positive experiences	Patient qualitative and quantitative surveys Medical Record Patient registration system
*How effective was the model of care in increasing stakeholder engagement in Direct to Psychology (for staff) and digital intervention referrals (for staff and referrers)?*	**Adoption – engagement with and willingness to implement the new model of care**	• Percentage of patients referred to Psychology who were eligible for Direct to Psychology are referred to this pathway **Secondary outcomes** *Staff and Referrer satisfaction with digital intervention* • Staff and referrer reported ease of access to digital intervention • Acceptability and relatability of the online program/service provided including: i. motivation to refer patients to online treatment (diversion from public hospital services for insomnia treatment) ii. understanding of intervention materials iii. percentage of referrers and staff who would engage with online treatments in their standard care iv. perceived change in understanding of insomnia management	> 80% patient meeting inc/excl criteria are referred appropriately > 90% staff and referrers report positive experiences > 90% staff and referrers report they are ‘somewhat motivated’, ‘very motivated’ or ‘extremely motivated’ to prescribe the digital intervention in their practice	Staff and referrer qualitative and quantitative surveys Medical Record Patient registration system
*Was the model was delivered as intended?*	**Implementation -**consistency and fidelity of delivery as intended and the time and cost of the intervention	• % of model of care elements delivered as per protocol • Differences in % of model of care elements delivered as per protocol compared between participating intervention staff • Differences in patient-related outcomes (%MCID achieved) compared between participating intervention staff • Number of psychology-led discharges from Direct to Psychology pathway (diversion from medical pathway) • Number of occasions of service per psychology resource (staffing) available comparing the ‘old’ and ‘new’ model of care • Direct service costs versus revenue generated for new and review consultations of the ‘new’ model of care compared to the ‘old’ model of standard care	> 90% intervention components are delivered as per the protocol Implementation adaptations are reported at dissemination No significant difference in % model of care elements delivered between intervention staff No significant difference in MCID achieved between intervention staff The new model of care is cost effective, less resource intensive and more time efficient than the old model of care	Medical Record Patient registration system Document review
*How sustainable is this model of care*,* how well can the model of care continue to operate into the future?*	**Maintenance – long term effects of the program**,** model is business as usual**	• % components of model still operating 6 months post completion of the study • Description of which components of the model are still operating 6 months post completion of the study • Demand for the service – number of Direct to Psychology referrals and patient assignment to the different ‘levels’ of the model 6 months post completion of the study • Evidence of scale and spread of similar models across other services internal and external to the health provider	> 95% of the model is still operating 6 months post completion (July 2026) Number of Direct to Psychology referrals and patient assignment to treatment levels are sufficient to justify ongoing service provision	Document review

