There is significant evidence for Cognitive Behaviour Therapy for insomnia (CBTi) as the first-line treatment for insomnia [2, 11], recommended by both the American Academy of Sleep Medicine (AASM) and the Australasian Sleep Association (ASA), as CBTi has extensive Level I evidence for longitudinal gains in insomnia resolution [8, 12]. Internet-delivered CBTi has been extensively investigated in the clinical literature, with systematic reviews and meta-analyses demonstrating that these first-line interventions are just as effective as face-to-face modalities in the general population for those with insomnia of low to moderate severity [6, 13–18]. “Stepped care” refers to a service delivery model allowing a relatively scarce healthcare resource to be applied in a cost-effective way to achieve timely and effective clinical care [15, 19]. CBTi is a well validated intervention with demonstrated amenability to a Stepped Care model, where patients are assessed for entry to first-line manualised and online treatment programs, increasing to progressively more time, cost and expertise intensive levels ‘upstream’ where there is an incomplete therapeutic response to a first-line intervention, or when clinical complexity demands a more intensive intervention step within the care pathway.

In our tertiary public hospital multidisciplinary sleep service, the current model of care (MoC) relies on a “medical-first” referral pathway which overburdens specialist medical services and delays care to evidence-based psychological treatment. Furthermore, intensive 1:1 interventions with the sleep psychology team results in bottlenecks in patient access. These pressures require implementation of systematised and innovative models of care, delegation to junior staff, and utilisation of time efficient (e.g., group delivery) and technological solutions designed to improve service efficiencies, effectiveness of care, and to maintain or improve patient reported experience and outcomes. A protocol for the evaluation of a new Direct to Psychology Stepped Care Model to address these pressures is presented, which utilises a direct referral pathway as well as stepped care approaches to service delivery. This study has a particular interest in exploring the feasibility and acceptability of digital intervention as a first-line treatment option.

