#### Direct to psychology stepped care

All patients referred to sleep psychology will complete an initial assessment according to Diagnostic and Statistical Manual (DSM-V-tr) and International Classification of Diseases (ICD-11) criteria [26, 27], including outcome measures (see *Measures).* For patients referred ‘Direct to Psychology’ additional measures will manage any potential risks associated with psychology as first contact within the model due to potential ‘missed’ medical clinical indications. These measures will include screening tools for Obstructive Sleep Apnoea (OSA) (using items from the STOP-BANG [28] and Berlin Apnoea [29] Questionnaires), hypersomnolence disorders (using items from the Cataplexy Questionnaire [30] and questions related to the presence of neuromuscular conditions, respiratory conditions and driving risk.

The inclusion criteria for Direct to Psychology criteria as defined in stakeholder co-design activities [24] include;

(i)being referred for insomnia and/or sleep psychology, and/or(ii)suboptimal adherence to OSA treatment including continuous positive airway pressure therapy (CPAP) or mandibular enhancement splint (MAS) if medical management has been already optimised.

Exclusion criteria include;

(i)significant new/changed sleep disordered breathing (or identified significant sleep disordered breathing)(ii)highly comorbid patients (e.g., neuromuscular conditions/weakness, respiratory conditions), diagnosis of hypersomnia/question of central disorder of hypersomnolence(iii)category 1 (urgent) referrals(iv)driving risk.

Patients identified as meeting the inclusion and exclusion criteria will proceed with Psychology-first intervention as indicated. Patients who meet the exclusion will be redirected back to the Standard Care model and may be re-triaged by the attending medical officer based on the additional information gleaned from the psychological assessment.

Patients progressing to psychological treatment will be matched to the appropriate treatment level. Depending on patient engagement and participation with the treatment level, as well as clinical outcomes on key assessment measures; discharge, on-referral and/or entry to another intervention level will be provided. The proposed steps of care in the new model are outlined in Fig. 2.

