## Discussion

The overarching goal of this project is to implement and report on changes in the service model in our multidisciplinary sleep service, specifically a new model of care that incorporates a “Direct to Psychology Insomnia” referral pathway, that includes a “Stepped Care” treatment approach that utilises digital, group therapy, and intern and senior therapist-led interventions. Other multidisciplinary teams have envisioned similar Allied Health-led referral pathway plans to beneficial effect [43, 44]. Results from this study will highlight the potential for Direct to Psychology referral pathways in reducing the clinical burden on physicians and expediting patient access to first-line treatment for insomnia. Patient outcomes, satisfaction, and service-based evaluation tools are embedded in this project to compare the model of care to treatment as usual. We anticipate that if shown to be acceptable, the findings from this study will inform future iterations and enhancements to the model of care, including the scalability to apply the model to other services.

Streamlining sleep psychology interventions into a stepped care treatment approach will allow patients to access the appropriate level of care based on their level of acuity and clinical presentation, with the model being flexible enough for patients to be expedited to more resource intensive levels of care based on treatment response. The new model of care will utilise technology as part of a Stepped Care model to provide a platform for more efficient service delivery, backed by expert clinician oversight in order to provide care to more patients within existing resources. We expect the new evidence-based model of care will substantially reduce wait times for patients and provide timely access to effective Psychological treatment, resulting in non-inferior clinical outcomes. We posit that this dynamic approach to sleep disorder management will result in better patient access and outcomes, leading ultimately to reduced societal burden from reduced productivity and health care costs due to untreated sleep disorders.

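### Adequate treatment at each level and digital completion are related only to age, sex, location and presenting issue; baseline ISI, already collected, is left out

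*Protocol article*

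**What the plan says.** In the protocol article, Table 1 (RE-AIM evaluation framework) names the same four traits in four places that concern treatment level or digital care:

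- Reach, accepting or declining digital care: "Differences in patient characteristics (age, sex, geographical location, presenting issue) between those agreeing to digital compared to those declining".
- Reach, level assignment: "Number of patients and patient characteristics (age, sex, geographical location, presenting issue) of those assigned to each treatment level".
- Effectiveness, completion of digital care: "Differences in patient characteristics (age, sex, geographical location, presenting issue) between those who complete the digital intervention compared to those who do not complete".
- Effectiveness, adequate treatment, listed under primary outcomes and labelled a moderation analysis: "Differences in patient characteristics (age, sex, geographical location, presenting issue) between those who are adequately treated at each level of the new model of care".

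None of the lists is introduced as an example, and none names a severity measure. Presenting issue is the type of problem, not how severe it is.

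Three other places bear on the omission:

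- Under Direct to psychology stepped care, "All patients referred to sleep psychology will complete an initial assessment", and that assessment includes the outcome measures. Under Patient-related outcomes these are the ISI, DASS-21, K10 and EQ-5D-5L.
- The Background describes internet-delivered CBTi as "just as effective as face-to-face modalities in the general population for those with insomnia of low to moderate severity".
- The Discussion says that patients will "access the appropriate level of care based on their level of acuity and clinical presentation".

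Under Patient-related outcomes, adequate treatment means discharge by the treating clinician with measures showing reliable change. Table 1 sets the standard as the MCID reached by more than 80% of patients at each level. For the ISI, the article puts the minimally important difference at a change above 8.

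**The concern.** Whether a patient passes a fixed change threshold depends on where the patient started. If baseline ISI differs by location, age, sex or presenting issue, those traits will be associated with success even when they have no bearing on response to treatment. An analysis presented as moderation would then suggest that a level works less well for, say, one location, when the groups only started at different scores.

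Completion has no change-score problem, but it does have a confounding one. The plan's own rationale for digital care is limited to low to moderate severity, so severity is a plausible reason for not finishing. If it is, comparisons on four other traits either miss it or show it indirectly through a correlated trait.

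What is at stake is the reading of who does well at which step, not the conclusion on non-inferiority or access.

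**Working it through.** The plan states no figure that depends on this choice, so there is nothing to reproduce. The check has three parts.

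**1. Arithmetic of the threshold (documents only).** ISI scores are whole numbers, so a change above 8 means a fall of at least 9.

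- Baseline 8 or less: the threshold cannot be reached.
- Baseline 11: the score must fall to 11 − 9 = 2 or below.
- Baseline 22: the score must fall to 22 − 9 = 13 or below.

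**2. How large a spurious difference could be (assumed inputs).** The documents give no ISI means or SDs. Assume a mean reduction proportional to baseline (35%, 45% or 55%) and an SD of change of 5. With a continuity cut at 8.5, the chance of success at baseline b and relative reduction r is

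P = 1 − Φ((8.5 − r·b)/5).

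At r = 0.45:

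- b = 12: (8.5 − 5.4)/5 = 0.62, so P = 0.27.
- b = 22: (8.5 − 9.9)/5 = −0.28, so P = 0.61.

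Now take two location groups with the same relative benefit, assumed mean baseline ISI of 15 and 18, and SD 4 in each. Averaging over baseline, the SD of change becomes √(25 + (4r)²), and the success rate is about 1 − Φ((8.5 − r·mean)/SD). The last two columns come from a simulation that also caps the change at the baseline score.

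| Mean reduction | Closed form, mean 15 | Closed form, mean 18 | Simulated, 15 v 18 | Gap (points) |
|---|---|---|---|---|
| 35% | 0.27 | 0.34 | 0.260 v 0.334 | 7 |
| 45% | 0.37 | 0.47 | 0.364 v 0.469 | 10 |
| 55% | 0.48 | 0.60 | 0.472 v 0.599 | 13 |

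By construction location has no effect of its own. The whole gap comes from the 3-point baseline difference.

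**3. Uptake of digital care (assumed inputs).** Suppose 80% accept, severity alone drives declining, and the odds ratio is 2.0 per SD. Decliners are then about 0.64 SD more severe than acceptors, which the listed comparisons would not show. A listed trait correlated 0.2 to 0.4 with severity would show an apparent difference of about 0.13 to 0.26 SD. Over odds ratios of 1.5 to 3.0 the ranges are 0.39 to 0.93 SD for severity and 0.08 to 0.37 SD for the trait. With no correlation, no listed trait differs and the severity effect is not seen at all.

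**The case against.** The strongest reply is that nothing in Table 1 is false. It is an indicator table in a condensed article, and the Statistical analysis section says that other variables of interest and potential confounders will be tested in multivariable models. That wording would allow baseline ISI. It follows the wait-time analysis, however, and names only patient characteristics and diagnosis, while Table 1 spells out its traits without severity. The reply therefore lowers the weight of the point but does not remove it.

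Several further objections stand:

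- The acceptance and assignment items are descriptive. Reach concerns numbers, proportions and representativeness, and the four traits are a reasonable profile for that. There, adding baseline ISI is only an improvement in reporting.
- The illustration of success rests on invented inputs. No passage says that severity differs by location. The ISI threshold also simplifies adequate treatment, which involves discharge and more than one instrument.
- An unadjusted difference is still a true description of who passes the threshold. It misleads only when read as differential response.

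A reader might also infer three stronger conclusions that the documents do not support. One is that the study cannot show whether milder patients take up digital care. It could, because ISI is collected at initial assessment and at each digital session. Another is that severity is the single trait that decides the level. The article also cites clinical complexity, incomplete response and comorbidity, and the assignment criteria sit in cited work and in a figure that is not shown. The third is that these comparisons will steer level assignment, which no passage says.

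**Conclusion.** The point holds as a modest one. Relating adequate treatment and digital completion to the four listed traits without baseline ISI leaves differences that may partly reflect starting severity. It is firmest for adequate treatment, where dependence on the baseline follows from the change threshold itself. For completion it rests on severity being a plausible reason for not finishing.

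The size is not known. The gap of about 7 to 13 points assumes a 3-point difference in mean baseline ISI, proportional benefit of 35% to 55%, an SD of change of 5 and a baseline SD of 4. With no baseline difference between groups there is no spurious gap. No sample size or power figure changes, and the old-versus-new comparison does not use these lists.

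**What to change.** In Table 1, Effectiveness, state that when adequate treatment or digital completion is related to age, sex, location or presenting issue, the model will include baseline ISI as a continuous covariate. Report the unadjusted and adjusted differences side by side. Add baseline ISI to the characteristics reported for digital acceptors and decliners and for each treatment level. Report K10 or DASS-21 descriptively rather than as further covariates.

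The measure is already part of the initial assessment, so no data collection is added. The cost is one more covariate where groups are small. If all 110 patients expected in the post period were offered digital care and 80% accepted, there would be 110 × 0.20 = 22 decliners. If 80% of the 88 acceptors completed, there would be about 88 × 0.20 ≈ 18 non-completers. Groups of that size support few covariates, which is why baseline ISI alone should enter the models. Where all traits cannot be fitted together, fit each trait with baseline ISI only and present the results as exploratory estimates with confidence intervals.

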#### Staff

Clinicians and team members, who agree to participate in our surveys.

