#### Referrers

All referrers linked to patients included in the project, who respond to our surveys.

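### The >90% positive-experience targets name whole groups, but non-respondents (by definition) and patients who never engage with the digital program (probably) are under-represented in the count

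*Protocol article*

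**What the plan says.** In Table 1 (RE-AIM), the Effectiveness row gives the target for patient satisfaction with the digital intervention as "> 90% patients report positive experiences". The Adoption row gives "> 90% staff and referrers report positive experiences", and a second >90% target for staff and referrers who are at least somewhat motivated to prescribe the program.

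The Participants section defines the two professional groups by their response. Staff are "Clinicians and team members, who agree to participate in our surveys"; referrers are "All referrers linked to patients included in the project, who respond to our surveys".

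For patients, the section on patient, staff and referrer satisfaction sets the population as "for those patients assigned to digital intervention in the new model of care". Acceptability and relatability "will be measured via post-intervention questionnaires delivered to patients and staff via a RedCap survey". The same section sends a questionnaire to "All multidisciplinary staff of the Sleep Disorders Centre employed during the new model of care implementation phase".

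The Level 1 section describes two branches after the 2-week call. Patients who are engaging well get a further call six weeks later, timed to the end of treatment, at which outcome measures are collected. Patients who have not engaged by week 4 discuss the reasons and are offered discharge, on-referral or another level; no survey is mentioned there. The Reach row of Table 1 has its own targets for acceptance, start within 4 weeks and completion, the last being "> 80% patients complete digital intervention".

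**The concern.** A pass mark is fixed for a group named as a whole, while the people counted towards it are partly self-selected.

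For staff and referrers the selection is in the definition. A referrer who ignores the survey is not a participant and leaves the denominator. Yet the Adoption domain is about engagement with the model, and silence may be a sign of low engagement.

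For patients the selection comes from timing. A questionnaire placed after the intervention suits those who reach its end. A patient who never starts and is moved or discharged at week 4 has no described point at which to answer.

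Digital acceptability is a declared particular interest of the study. The Discussion says that a finding of acceptability will inform later versions of the model and its extension to other services. These targets are the yardstick for that finding.

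**Working it through.** **What can be reproduced.** The >90% target is a benchmark. It comes with no sample size, response rate or confidence bound, so there is no figure of the plan's own to reproduce. Two checks show what the choice of denominator can do.

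**Check 1: bounds over everyone assigned or invited.** Let r be the share who answer and q the positive share among those who do not. If exactly 90% of respondents are positive, the share over everyone is 0.90 × r + q × (1 − r). Neither r nor q is in the article, so both are assumptions.

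| r | q = 0 | q = 0.5 | q = 1 |
|---|---|---|---|
| 0.8 | 72% | 82% | 92% |
| 0.6 | 54% | 74% | 94% |
| 0.4 | 36% | 66% | 96% |

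Example: 0.90 × 0.8 + 0.5 × 0.2 = 0.72 + 0.10 = 82%. The direction depends on q: for q below 0.90 the respondent figure flatters the program, and for q at or above 0.90 it does not.

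**Check 2: chance of meeting the patient target.** Assumptions: 50 patients assigned, only completers answer, and 95% of completers are positive. Non-completers are positive at rate q, and in the all-assigned column all 50 answer. With n completers, the expected all-assigned share is [0.95 × n + q × (50 − n)] / 50. Exceeding 90% needs at least 46 of 50, 37 of 40, 37 of 41 or 32 of 35. Probabilities are exact binomial, or for all assigned the sum of two binomials.

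| Completers | q | Expected share, all assigned | P(>90%), completers only | P(>90%), all assigned |
|---|---|---|---|---|
| 40 of 50 | 0.20 | 80% | 0.86 | 0.001 |
| 40 of 50 | 0.50 | 86% | 0.86 | 0.11 |
| 40 of 50 | 0.80 | 92% | 0.86 | 0.63 |
| 40 of 50 | 0.95 | 95% | 0.86 | 0.90 |
| 41 of 50 | 0.50 | 86.9% | 0.95 | 0.16 |
| 35 of 50 | 0.50 | 81.5% | 0.90 | 0.02 |

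The row with 41 completers matters most. Completion is 41/50 = 82%, so the Reach completion target is met, yet the choice of denominator moves the pass probability from 0.16 to 0.95. The rows with 40 and 35 completers (80% and 70%) would already miss that target, which requires more than 80%. In the row with q = 0.95 there is no inflation.

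**Counting non-response as not positive.** Even if every respondent is positive, the share over all invited then cannot exceed r. At r of 0.90 or lower a target above 90% cannot be met.

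**The case against.** The case on the other side is substantial for patients.

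- A reader might infer that digital dropouts are excluded from the patient target. The article does not say so. It names those assigned to digital treatment, does not limit the questionnaire to completers and fixes no patient denominator. The Statistical analysis section speaks of post-implementation surveys, which need not depend on finishing the program. The later call for patients who were engaging well at 2 weeks is not conditional on completion, so some who stop midway still have a contact. This stands: under-representation is likely, not stated.
- A reader might also infer that the acceptability rule passes too easily. That requires non-respondents to be less satisfied, and the article offers no evidence of this. Barriers to engagement need not mean dissatisfaction. This stands too.
- Abandonment appears elsewhere in Table 1, in the three >80% Reach targets and in the comparison of completers with non-completers on patient characteristics. This stands in part: 82% completion would satisfy Reach and still leave room for a misleading experience figure. No response-rate target exists for staff or referrers.
- For staff and referrers, the target can be read as applying to participants as defined, that is, to respondents. All centre staff are sent a questionnaire, so a staff response rate can be calculated. But the target is worded over the whole group, and the article does not commit to showing the rate beside it.
- These are secondary benchmarks with no test attached, and detailed handling of non-response may sit in the full protocol or analysis plan. That limits the weight of the point. It does not remove the mismatch between the participant definitions and the wording of the targets.

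**Conclusion.** The point holds in a limited form. For staff and referrers, non-respondents leave the denominator by definition while the targets are worded over the whole groups. For patients, the population is everyone assigned to digital treatment, but the measurement is post-intervention and no survey point is described for those not engaged by week 4; they are likely to be missed.

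The acceptability figures may therefore be too favourable, provided that those missing are less satisfied. The size cannot be established from the article. The calculations show a range from no inflation (equal satisfaction) to a pass probability of 0.86 instead of 0.11 (50 assigned, 80% completing, 95% and 50% positive), all on assumed rates. It deserves correction because acceptability feeds the decision on scaling, but it concerns secondary, descriptive targets.

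**What to change.** 1. Offer the patient survey, limited to the items that apply, to everyone prescribed the digital program when their digital episode ends for any reason, including at the week-4 contact that is already planned.
2. State the denominators in Table 1: all patients prescribed the program, and all staff and all referrers sent the survey. Report the response rate for each group.
3. Show completers and non-completers separately.
4. Word any respondent-only result as applying to those who responded.
5. Give the count with non-response treated as not positive as a sensitivity bound only. As the pass rule it would make the target unattainable at a response rate of 90% or lower and would confuse silence with dissatisfaction.

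The cost is a change to the survey trigger and to the wording of Table 1, with slightly more survey administration. The headline may also be less favourable.
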